#### Adherence

The number of physiotherapy visits and telephone coaching calls, as well as the timing and duration of the calls, will be recorded. At 3, 6, 9, 12, 15 and 18 months, participants in both groups will be asked by postal questionnaire how many times they did their home exercises in the previous 2 weeks (out of a maximum of 6 sessions). They will also be asked to rate their adherence to their home exercise program over the previous 3 months (from ‘not at all’ to ‘completely as instructed’) using an 11-point numeric rating scale and to rate their change in physical activity level since the start of the study using a 7-point Likert scale (from ‘much less’ to ‘much more’. Physiotherapists and telephone coaches will also rate the participant’s adherence to the 6-month program using an 11-point numeric rating scale.

#### Adverse events, harms and use of health services/co-interventions

Information on adverse events, harms and direct health care costs and direct non-health care resources will be collected for each 3 month period during the study using log sheets given prospectively and collected at 3, 6, 9, 12, 15 and 18 months. Missing log sheets will prompt a phone call to collect the data retrospectively. Harms are adverse events that can be attributed to the intervention (home exercise program or additional physical activity). The adverse event log sheet will ask duration (days) of the problem and whether any treatment was sought for the problem regardless of cause.

Direct health care costs will include costs of physiotherapy attendance, additional health provider visits (doctors, specialists, other health care professionals), investigative procedures, purchase of prescription and over the counter medication, and hospitalization. Direct non-health care resources will include number of lost days from work.

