### Blinding

Outcome assessment comprises self-reported questionnaires that will be completed by participants at home and returned to investigators by mail or email. The research assistants entering the data will be blinded. The physiotherapists, telephone coaches and participants are by necessity unblinded. The statistician will be blinded to group allocation until completion of the statistical analyses.

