### Interventions

#### Physiotherapy only

Participants will visit a physiotherapist for five 30-minute sessions over the 6-month intervention period: in weeks 1, 3, 7, 12 and 20. The physiotherapist will prescribe a home exercise program and advise the participant to increase their levels of general physical activity. Five physiotherapy visits was chosen as this number should be able to achieve improvements in pain and function [17] and importantly has translational potential into the Australian health setting given that the Federal Government Medicare scheme can currently fund up to five visits per annum to an allied health professional for patients with a chronic problem such as OA.

Over the five sessions, the physiotherapist will perform standardised assessment/re-assessments, develop a home exercise program and promote increased levels of general physical activity, including aerobic activity such as walking and incidental physical activity. The physiotherapist will also assist the participant to gain knowledge about OA and the benefits of physical activity. Participants will receive an information booklet which covers the following topics: condition and treatment information, exercise and physical activity, pain management, benefits of weight loss, relapse prevention and management, and facilitators for change (http://bit.ly/KaPPTW). They will also receive exercise handouts demonstrating the home exercises, a pedometer as an optional self-monitoring and motivational tool, and log sheets to record exercise and other physical activity if desired.

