**Side stepping**	Weight-bearing	Crab walk (side stepping) with resistance band around thighs or ankles	
**Hip abduction dips**	Weight-bearing	Hip abductor dips (standing on affected leg, lower non-affected leg by frontal plane pelvic tilting)	

A brief assessment will be performed by the physiotherapist at each physiotherapy session in order to ascertain any adverse effects (if any) that may have occurred with home exercises and to check quality and form of exercise performance. Progression of exercises is an essential component of the program and the findings from the assessment will help guide physiotherapists’ decisions regarding progression. Progression will be provided by varying the exercises including the type of exercise as well as the number of repetitions, load or degree of difficulty within an exercise. In order to gain strength, the level of effort experienced during each strengthening exercise will be self-rated as at least 5 out of 10 (hard) on a modified Borg Rating of Perceived Exertion (RPE) CR-10 scale designed specifically for strengthening exercise [45]. In addition, the resistance prescribed will aim to approximate a 10-repetition maximum level.

In order to minimise burden of exercise, only the study knee will be the focus of treatment and will be evaluated with respect to outcome measures. If participants have bilateral symptoms, the physiotherapist may choose exercises that are performed weight-bearing on both legs simultaneously to achieve bilateral strength gains within the constraints of the treatment protocol.

The physiotherapists will also discuss the disease-specific and general health benefits of increased levels of general physical activity, including both incidental physical and whole-body exercise. To facilitate increased incidental physical activity, an optional but strongly encouraged part of the physical activity intervention will be use of a pedometer. A pedometer (Omron HJ-005, Omron Healthcare Co, Kyoto, Japan) will be provided to each participant to allow them to monitor their incidental physical activity throughout the day, and receive immediate feedback on their progress towards general activity goals. Pedometers have been previously used successfully in OA populations for such self-monitoring and motivational purposes [18,25]. The physiotherapist will educate the participants in the use of the pedometer and discuss options for achieving increases in daily step count and setting relevant short-term goals.

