#### Physiotherapy plus telephone coaching

The physiotherapy intervention will be the same as for the physiotherapy only group and delivered by the same physiotherapists. The participants in this group will also receive a telephone coaching intervention aimed at improving their adherence to their home exercise program and increasing their levels of general physical activity through behaviour change support. They will receive additional written information that explains the behaviour change support process. Telephone coaching sessions will be delivered 6–12 times during the 6-month intervention period. Calls will occur in weeks 2, 4, 8, 13, 21 and 25. Up to six additional calls can be made at any time during the 6 months according to participant confidence in taking action to change physical activity behaviours, adherence level, and preferences, as determined by the telephone coach, physiotherapist and participant. The initial call length is expected to range between 30–45 minutes with the remaining call durations lasting between 15 and 30 minutes.

The behaviour change model used for the telephone coaching intervention is the HCA Model of Health Change (http://www.healthchangeaustralia.com/the-hca-model.htm). Health Change Australia has been providing professional development training and consultancy in using the HCA Model of Health Change in Australia (since 2006) and Canada (since 2010). They have trained over 5,000 health professionals who work in a variety of public and corporate health settings. The HCA model has been used by both private and state based organisations to provide telephonic coaching services.

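### The harms definition names only components given to both arms and omits telephone coaching, the one randomised component; it also rests on a causal judgement in an unblinded trial

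*Protocol article*

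**What the plan says.** The section on adverse events, harms and use of health services separates adverse events from a subset called harms: "Harms are adverse events that can be attributed to the intervention (home exercise program or additional physical activity". Events are gathered "using log sheets given prospectively and collected at 3, 6, 9, 12, 15 and 18 months", and "Missing log sheets will prompt a phone call to collect the data retrospectively". On content, "The adverse event log sheet will ask duration (days) of the problem and whether any treatment was sought for the problem regardless of cause". No difference between arms is described for any of this, and Table 1 gives the same log sheets and time points.

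The section on physiotherapy plus telephone coaching says: "The physiotherapy intervention will be the same as for the physiotherapy only group and delivered by the same physiotherapists". That arm then receives 6–12 coaching calls over the 6 months. The calls are meant to raise adherence to the home exercises and general physical activity. The Background gives the primary objective as evaluating the addition of coaching.

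The Blinding section says: "The physiotherapists, telephone coaches and participants are by necessity unblinded". The research assistants who enter data and the statistician are blinded. The article does not say who decides whether an event can be attributed to the intervention.

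**The concern.** The bracket in the harms definition spells out what the intervention means, and it lists only what both arms receive. The component under test is left out. Taken as written, an event attributed to the calls themselves can be logged as an adverse event but cannot be classed as a harm. Any later analysis that uses the protocol's term would inherit the gap.

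The events that do qualify must pass a causal judgement. Coaching can alter how a participant reads a symptom. Extra conversations about exercise and problems could lead more symptoms to be blamed on exercise. The coaches also cover pain coping and activity pacing, which could lead fewer to be blamed. A between-arm table of attributed harms could therefore show a difference that reflects attribution only, or hide one that is real.

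**Working it through.** The article states no figure for adverse events or harms, so there is none to reproduce. The sample size is built from pain and function alone, and no harms quantity enters it.

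**1. Components against the definition**

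| Component | Physiotherapy only | Physiotherapy plus coaching | Named in the harms definition |
|---|---|---|---|
| Home exercise | yes | yes | yes |
| Increased physical activity | yes | yes | yes |
| Telephone coaching | no | yes | no |

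The only row that differs between arms is the only row the definition omits.

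**2. Which coaching harms fall inside and outside**

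- Coaching leads to more exercise or activity, which leads to a flare or injury: inside, because the proximate cause is one of the two named items.
- Coaching leads directly to distress or burden: outside, because the cause is not named.

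**3. What differential attribution could do.** Write p for the true event risk and a for the share of events attributed. The harms proportion is p × a. The figures here are assumptions, not taken from the article: p = 0.30 in both arms, a = 0.50 in one arm and 0.60 to 0.70 in the other.

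- 0.30 × 0.50 = 0.15
- 0.30 × 0.60 = 0.18 and 0.30 × 0.70 = 0.21
- If the coached arm attributes more: 0.18/0.15 = 1.2 to 0.21/0.15 = 1.4
- If the coached arm attributes less: 0.15/0.18 = 0.83 to 0.15/0.21 = 0.71

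With equal p, the ratio is simply the ratio of the two attribution shares. The exercise shows the mechanism and does not estimate its size. An all-event comparison has no a in it and gives 0.30/0.30 = 1.0.

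**4. Contact is not ascertainment.** The Physiotherapy only section gives the common schedule: "Participants will visit a physiotherapist for five 30-minute sessions over the 6-month intervention period".

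- Contacts: 5 against 5 + 6 = 11 to 5 + 12 = 17, so 11/5 = 2.2 to 17/5 = 3.4 times.
- Contact minutes, using the stated call lengths: 5 × 30 = 150 in both arms. Calls add 30 + 5 × 15 = 105 (six calls, shortest) to 45 + 11 × 30 = 375 (twelve calls, longest). The ratio is 255/150 = 1.7 to 525/150 = 3.5.
- Scheduled log sheets: 6 in each arm, a ratio of 6/6 = 1.0. Four of the six (9, 12, 15 and 18 months) cover periods after the calls have ended.

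**5. Physiotherapy notes as an added source.** Physiotherapists make a brief assessment at each session in both arms "in order to ascertain any adverse effects (if any) that may have occurred with home exercises". Those notes may look like a balanced supplement to the logs. However, in the coached arm the physiotherapist must read the coach's entries, which include problems the participant has had, before each session. No such input exists in the other arm, so the notes are informed by an extra source on one side only.

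**The case against.** The strongest case on the other side has five parts.

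- **All adverse events are collected.** Leaving an event out of harms does not remove it from the adverse event log. This stands: the weakness lies in the definition and its use, not in data capture.
- **Coaching works through exercise and activity.** Its likeliest physical harms are therefore inside the definition, and randomisation lets them be compared. This also stands. A reader might infer that the harms comparison cannot answer the trial's question at all; the documents do not support that.
- **Psychological effects are measured.** The depression, anxiety and stress scale, the PHQ-9, pain catastrophising and fear of movement are collected in both arms at 0, 6, 12 and 18 months. This stands in part: a shift in mean scores could be seen. But the article presents these scales as possible mediators and measures of implementation, and they do not classify events.
- **No harms comparison is specified, and attribution procedure belongs in a full protocol.** This is fair. The hypotheses do not mention harms, and the article's silence on the assessor and the safety tables is not itself a fault. The wording of the definition is on the page, however, and is not missing detail.
- **The assessor might be blinded.** The article does not exclude this. Even so, a blinded assessor would be working from the accounts of participants who know their arm.

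A reader might also take the 2.2 to 3.4 contact ratio as a ratio of opportunities to record events, or assume that bias must inflate harms in the coached arm. Neither follows: scheduled collection is equal, and the direction is open.

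**Conclusion.** The point holds in a limited form. The definition omits the only randomised component, so harms attributed directly to coaching would not be counted as harms, while those acting through exercise or activity would. The attributed subset is also open to differential attribution of unknown direction and size. The ratios of 0.71 to 1.4 rest wholly on assumed risks and attribution shares.

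This is a modest flaw confined to safety reporting. It rests on reading the bracket as the full meaning of the intervention, and on the log capturing events whatever their cause, which is how the article describes the treatment-sought item. Primary outcomes, sample size and the collection schedule are unaffected.

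**What to change.** In the section on adverse events and harms:

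1. Add telephone coaching to the components to which a harm can be attributed.
2. State that the main between-arm safety comparison is all logged adverse events regardless of attribution, together with those for which treatment was sought. Report attributed harms as secondary.
3. Do not add events from physiotherapy notes to the between-arm count, because those notes draw on coaches' entries in one arm only.

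The cost is a few sentences. The comparison uses log sheets already scheduled alike in both arms, with no new visits or staff. If the log sheet has an attribution item, which the article does not show, it would need coaching as an option. The downside is that an all-cause count includes unrelated events and is less specific to the intervention. It removes the causal judgement but not the fact that participants who know their arm fill in the logs.

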### Economic Evaluation

The economic evaluation will assess the incremental cost of the physiotherapy plus telephone coaching intervention compared with physiotherapy only. The primary economic evaluation will report cost effectiveness at 18 months with secondary economic evaluations at 6 and 12 months. The incremental cost will be compared to the incremental benefits of treatment in terms of a clinically significant improvement in pain, a clinically significant improvement in function, and the difference in quality adjusted life years (QALYs). The incremental QALYs will be measured by the between group difference in the mean AQoL2 score over 6, 12 and 18 months. A social perspective on costs will be taken and will include resource use incurred both by health services and by the patient irrespective of payment source. Prospective self-reported direct health care use will be collected every 3 months using log sheets. Health care costs will be calculated from the utilisation data and published average unit costs for each item. The direct cost of the intervention will be based on physiotherapy charges per session and telephone coaching costs per person. The inclusion of time/productivity gains is controversial and the cost effectiveness ratios will be calculated with and without these “indirect costs”. Confidence intervals for incremental cost effectiveness will be calculated directly using non parametric bootstrapping. In addition we will calculate a cost effectiveness acceptability curve based for a range of hypothetical money values of outcomes [74]. This will be done using individual cost and outcome data over the 6, 12 and 18 months or, if adjustments for imbalance at baseline are necessary, using regression analysis [75]. As part of the economic evaluation we will survey participants at the 6, 12 and 18 month questionnaire about their satisfaction with the intervention including its value for money.

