**Secondary outcome measures**		
Average pain on walking in past week	11-point numeric rating scale (NRS)	0, 6, 12, 18 months
Pain in past 48 hours	WOMAC Osteoarthritis Index pain subscale	0, 6, 12, 18 months
Perceived change overall	7-point ordinal scale	6, 12 and 18 months
Perceived change in pain	7-point ordinal scale	6, 12 and 18 months
Perceived change in function	7-point ordinal scale	6, 12 and 18 months
Physical activity levels	Active Australia Survey	0, 6, 12, 18 months
	Physical Activity scale for the elderly (PASE)	0, 6, 12, 18 months
	7-day ActivPAL^TM^ physical activity recording	0, 6 months
Health-related quality of life	AQoL2 questionnaire	0, 6, 12, 18 months

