#### Health-related quality of life

Health-related quality of life will be measured using the Assessment of Quality of Life instrument version two (AQoL2). The AQoL2 has 20 questions that cover six dimensions of health-related quality of life including independent living, social relationships, physical senses, coping, pain and psychological wellbeing. The AQoL2 has strong psychometric properties and is more responsive than other quality of life scales [58,59]. Scores range from −0.04 (worst possible health-related quality of life) to 1.00 (full health-related quality of life). A clinically important difference in health-related quality of life can be defined as a change of 0.04 AQoL units [60].

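### The stated rule for incremental QALYs is a difference in mean AQoL2 score with no time dimension; followed literally, it gives a wrong cost per QALY at 6 months and at the primary 18-month horizon

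*Protocol article*

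**What the plan says.** The Economic Evaluation section of the protocol article sets the incremental cost of adding coaching against three effects: clinically significant improvement in pain, the same in function, and the difference in QALYs. For the third it gives a rule: "The incremental QALYs will be measured by the between group difference in the mean AQoL2 score over 6, 12 and 18 months". On horizons it says: "The primary economic evaluation will report cost effectiveness at 18 months with secondary economic evaluations at 6 and 12 months". On computation of the ratios and acceptability curve it adds: "This will be done using individual cost and outcome data over the 6, 12 and 18 months", with regression as the alternative if baseline imbalance calls for adjustment.

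The Health-related quality of life section describes AQoL2 as a score from −0.04 to 1.00, where 1.00 is full quality of life. It also gives a benchmark: "A clinically important difference in health-related quality of life can be defined as a change of 0.04 AQoL units". Table 1 schedules AQoL2 at 0, 6, 12 and 18 months. Health service use is logged every 3 months, so costs build up over each horizon.

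The article nowhere mentions an area under the curve, weighting by interval length, or multiplication by duration.

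**The concern.** A QALY has units of utility × years. A difference in mean AQoL2 score has units of utility only. The two agree numerically only when the mean is time-weighted and the horizon is exactly one year. The article's horizons are 0.5, 1.0 and 1.5 years, and the longest is the primary one.

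The rule therefore puts a cost that grows with the horizon over a benefit that does not. A steady utility gain would count as the same number of QALYs at 6 months as at 18. On the time-weighted reading, coaching looks too favourable at 6 months and too unfavourable at 18, so a time trend in cost per QALY could come from the definition alone. Any comparison with a money value per QALY, including the acceptability curve for that outcome, would carry the same error. The Discussion presents the economic evaluation as an aid to funding decisions, where cost per QALY is likely to be read at face value.

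**Working it through.** The article states no QALY or cost-per-QALY figure, so there is none to reproduce. The check compares the written rule with utility × years.

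**Inputs**
- Horizons T = 0.5, 1.0 and 1.5 years (Economic Evaluation).
- AQoL2 at 0, 6, 12 and 18 months (Table 1), so each interval is 0.5 years.
- Illustrative AQoL2 difference 0.04 (Health-related quality of life). Its use as a between-group difference, and the trajectories below, are assumptions.
- Incremental cost: not given. Assumed range 100 to 500 currency units per person.

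**QALY gain by the trapezium rule.** With between-group differences d0, d6, d12 and d18:
- 6 months: 0.25×d0 + 0.25×d6
- 12 months: 0.25×d0 + 0.5×d6 + 0.25×d12
- 18 months: 0.25×d0 + 0.5×d6 + 0.5×d12 + 0.25×d18

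For differences 0, 0.04, 0.04, 0.04:
- 6 months: 0.25×0.04 = 0.010
- 12 months: 0.02 + 0.01 = 0.030
- 18 months: 0.02 + 0.02 + 0.01 = 0.050

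**Reading A: time-weighted mean.** The rule gives area ÷ T:
- 0.010/0.5 = 0.020, 0.030/1.0 = 0.030, 0.050/1.5 = 0.033
- Ratio to the QALY gain is 1/T: 2.0, 1.0, 0.67
- Cost per QALY relative to the correct value is T: 0.5, 1.0, 1.5

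These factors depend on neither the trajectory nor the 0.04.

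In money, for a time-weighted mean difference of 0.04 over the horizon, the rule uses 0.04 at every horizon, while utility × years gives 0.02, 0.04 and 0.06:

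| Assumed incremental cost | Rule, any horizon | Correct, 6 months | Correct, 12 months | Correct, 18 months |
|---|---|---|---|---|
| 100 | 2,500 | 5,000 | 2,500 | 1,667 |
| 300 | 7,500 | 15,000 | 7,500 | 5,000 |
| 500 | 12,500 | 25,000 | 12,500 | 8,333 |

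**Reading B: simple mean of the follow-up scores, or the mean at the time point.** For 0, 0.04, 0.04, 0.04 both give 0.040 at every horizon:
- 0.040/0.010 = 4.0, 0.040/0.030 = 1.33, 0.040/0.050 = 0.80
- Cost per QALY is 0.25, 0.75 and 1.25 times the correct value

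Here the size depends on the trajectory. Ratio of the rule to the QALY gain at 6, 12 and 18 months:

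| Differences at 0, 6, 12, 18 months | QALY gain | Simple mean | Time-point mean |
|---|---|---|---|
| 0, 0.04, 0.04, 0.04 | 0.010, 0.030, 0.050 | 4.0, 1.33, 0.80 | 4.0, 1.33, 0.80 |
| 0, 0.04, 0.02, 0 | 0.010, 0.025, 0.030 | 4.0, 1.20, 0.67 | 4.0, 0.80, 0 |
| 0, 0.02, 0.03, 0.04 | 0.005, 0.0175, 0.035 | 4.0, 1.43, 0.86 | 4.0, 1.71, 1.14 |

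On reading B, 12 months is no longer safe. With a time-point mean, even the direction of the error at 18 months can change.

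**The case against.** The strongest reply is that the sentence is loose rather than wrong. The effect has just been named as a difference in QALYs. The word mean could refer to averaging across participants, and over could mean accumulated over each period, as it must for the costs described in similar terms later in the section. A health economist might compute an area under the curve regardless. This reading is possible and cannot be excluded, so a reader should not infer that the trial's cost per QALY will certainly be wrong. But the text does not say it, and a prespecified rule should not depend on the analyst departing from its words.

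A second reply is that an article leaves computational detail to a fuller plan. That would answer a complaint about a missing trapezium rule. It does not answer this point, because the article does state a rule and the rule has the wrong units.

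Several stronger inferences are tempting, and the documents do not support them:
- *That the economic hypothesis as a whole fails.* QALYs are one of three effect measures, and H4 relates costs to the intervention's effects generally. The pain and function ratios are untouched.
- *That results cannot be compared across horizons at all.* On the time-weighted reading the error is the known factor T. It can be undone, and it leaves the sign of the QALY difference unchanged.
- *That the plan ignores baseline or weights visits equally.* It never specifies a simple or equally weighted mean, and it provides for regression if baseline imbalance needs adjustment. That provision does not supply the missing time dimension.

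**Conclusion.** The rule is wrong as written. The severity is moderate and confined to the economic evaluation.

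The firm part is the dimension: a mean AQoL2 difference is not a QALY, and no text in the article converts it. With a time-weighted mean, cost per QALY is 0.5, 1.0 and 1.5 times the correct value at 6, 12 and 18 months, whatever the data. With a simple or time-point mean, the error generally extends to 12 months and its size rests on an assumed trajectory, so the 4, 1.33 and 0.80 figures are illustrations, not predictions.

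Both results assume the sentence is applied literally. No reported result is shown to be wrong. The clinical primary outcomes, the sample size and data collection are unaffected.

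**What to change.** Replace the sentence on incremental QALYs in the Economic Evaluation section with:

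> Each participant's QALYs are the area under the AQoL2 utility curve from baseline by the trapezium rule, in years (6 months: 0.25×U0 + 0.25×U6; 12 months: 0.25×U0 + 0.5×U6 + 0.25×U12; 18 months: 0.25×U0 + 0.5×U6 + 0.5×U12 + 0.25×U18). The incremental QALY is the between-group difference in mean QALYs, estimated by regression adjusting for baseline AQoL2.

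The last clause makes standing an adjustment that the plan now makes conditional on imbalance. U0 enters the area with weight 0.25 at every horizon, so a chance baseline difference would otherwise pass into the QALY difference.

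The cost is one sentence of wording. All four AQoL2 assessments are already scheduled, so no new data, visits or participants are needed. If a fuller analysis plan already defines QALYs this way, the article's sentence need only be brought into line with it.
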